**Fig. 1 Fig1:**
[figure not shown]
CONSORT diagram of the ICEAGE trial. Abbreviations: DB&C deep breathing and coughing, PPC postoperative pulmonary complications, HRQOL health-related quality of life

### Trial setting

The three participating centres represent a range of hospital types in Australia. The Launceston General Hospital (Launceston, Tasmania, Australia) is a regional primary referral hospital; the Princess Alexandra Hospital (Brisbane, Queensland, Australia), a metropolitan primary referral hospital; and Northeast Health Wangaratta (Wangaratta, Victoria, Australia), a sub-regional secondary referral hospital, are all government-funded, university-affiliated, teaching hospitals.

### Eligibility and exclusion criteria

Local investigators will screen daily surgery lists and recruit eligible patients from the ICU and wards at participating hospitals. Eligible patients will be adults over 18 years having open emergency abdominal surgery. This is defined as time-critical surgery (within 48 h of decision to operate) for a condition that is an immediate or intermediate threat to life or organ survival, involving at least one incision greater than, or equal to, 5 cm anywhere in the abdomen and through the fascia, for an existing hospital patient or a person admitted through the emergency department and requiring at least an overnight stay. Exclusion criteria are as follows: procedures solely involving inguinal hernia repairs, appendectomies, organ transplantation, thoracic, or gynaecological surgery; a PPC diagnosis anytime in the 24 h prior to eligibility screening; a pre-existing condition where the patient is unable to stand upright and ambulate for 1 min without a seated rest; severe cognitive impairment; unable to understand spoken English without the assistance of an interpreter (as determined by the research assistant, site investigator or ward physiotherapist performing eligibility screening); within 7 days of elective abdominal surgery; planned repeat surgery within 5 days of emergency procedure; approaching imminent death or withdrawal of medical treatment within 48 h of their surgical procedure; medical orders not to participate in early active rehabilitation; patients unable to be randomised by the research team within 48 h of surgery; enrolment in another clinical trial with similar endpoints; and previous enrolment in ICEAGE.

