### Outcome measures

#### Primary outcome

The primary outcome is the first occurrence of a PPC within the first 14 postoperative hospital days. PPCs will be defined by the Melbourne Group Score (Table 3) which is reliable, valid [27, 28], sensitive to interventions [16], and has high inter-rater reliability [29]. It has eight clinical criteria: four factors relating to symptoms and four to diagnostic markers. A PPC will be diagnosed when four or more factors are present at any time from midnight to midnight on one postoperative day. The day a PPC is first diagnosed is the day of onset for purposes of time-to-event analysis.

**Table 3 Tab3:** PPC diagnostic criteria—Melbourne Group Score Version 3

When four or more of the following criteria^*^ are present anytime in the 24-h period 00:01 to 24:00 on a single postoperative day: 1. New abnormal breath sounds on auscultation different to preoperative assessment^+^ 2. Production of yellow, green, or brown sputum different to pre-morbid status^+^ 3. Pulse oximetry oxygen saturation (Sp0_2_) < 90% on room air or FiO2 on 0.21 on more than one consecutive postoperative day^**^ 4. Raised maximum tympanic temperature ≥ 38 °C on more than one consecutive postoperative day 5. Chest radiograph report of collapse/consolidation^# ***^ 6. Presence of infective organisms on sputum culture report^***^ 7. White cell count > 11 or < 3 8. Physician’s diagnosis of postoperative pulmonary complication (e.g. atelectasis, pneumonia, AECOPD, respiratory failure, upper respiratory tract infection) OR prescription of an antibiotic specific for respiratory infection	

*Abbreviations*: *PPC* postoperative pulmonary complications, *SpO2* pulse oximetry, *FiO2* fraction of inspired oxygen, *AECOPD* acute exacerbation of chronic obstructive pulmonary disease, *PEEP* positive end expiratory pressure, *CXR* chest X-ray

*If a blinded physiotherapist, nurse, or physician documents in the medical record the occurrence of a criterion, it can be taken as a positive finding. If no documentation present, a blinded assessor is required to assess this directly

^+^If no preoperative assessment or documentation assume normal at baseline

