**For ventilated patients, if FiO_2_ ≥ 0.5 or PEEP ≥ 8, assume criterion 3 is present (do not alter FiO_2_), for all other patients set FiO_2_ to 0.21 and observe SpO_2_ for 2 min. If SpO_2_ drops below 90%, immediately reinstate previous FiO_2_. If not permissible to alter ventilation parameters, assume positive

^#^If no written report for a CXR is available and a patient has three other positive signs, a masked senior physiotherapist or ward medical officer is to be contacted to report verbally on the available CXR

***When there are no daily measures of CXR or sputum sampling, carry over a positive finding to the next consecutive postoperative day

Participants are assessed prospectively and daily for a PPC by a blinded assessor until the seventh postoperative day. From the 8th to the 14th postoperative day, additional PPC assessments are performed only as clinically suspected based on signs or symptoms of respiratory system deterioration reported within the medical record. To reduce the potential for missing data, retrospective collection of PPC data from the medical record will be permitted when a patient or assessor is unavailable for PPC assessment. Diagnostic components (chest X-ray (CXR), white cell count, sputum microbiology) are recorded only if results are available. All medical officers are masked to group allocation, and these diagnostic tests are ordered only as clinically indicated, and not routinely for the purposes of the ICEAGE trial.

For this trial, modifications have been made to reduce delays to possible diagnosis of a PPC (Table 3). An automatic positive threshold for the hypoxemia criterion has been set for ventilated patients; a positive CXR and/or sputum sample finding can be carried over to the next postoperative day if serial testing was not performed; a CXR can be verbally reported by a blinded senior respiratory physiotherapist or physician, rather than awaiting a radiologist report; and when three factors (out of a possible eight) are present, the blinded site investigator or ward physiotherapist will discuss the option of further diagnostic testing to confirm PPC with the participant’s treating physician. Additionally, patients with three out of eight criteria will be assessed twice daily for any clinical deterioration.

Any suspected PPC will be confirmed by a blinded senior physiotherapist, and the participant will then receive respiratory treatment as determined by the ward physiotherapist.

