### Protocol endpoints

Treatment protocols will be ceased when:Participant is discharged or transferred from the primary treating hospital.Participant becomes deceased or death is expected within next 7 days.Participants meet a threshold score to trigger discharge from physiotherapy treatment^18^. This criterion is delayed for the first five postoperative days for intervention participants.A confirmed PPC diagnosis ceases the respiratory treatment protocol. Respiratory treatment is then provided at the discretion of the ward physiotherapist. Participants remain being treated with the rehabilitation protocol as per group allocation.A confirmed referral for additional sub-acute rehabilitation services ceases the ambulation or early rehabilitation protocol. Rehabilitation is then provided at the discretion of the ward physiotherapist. Participants remain being treated with the respiratory treatment protocol as per group allocation.

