##### Primary outcome

The absolute and relative rates of PPC in the trial groups will be estimated using multivariate robust random effects Poisson generalised linear regression to allow assessment of binary outcomes with or without adjustment for potential confounding variables (incidence rates and rate ratios, 95% confidence intervals, *p* values). Treatment centre will be treated as a fixed variable in multi-level models. In addition, the effect of time from the end of surgery/anaesthesia to commencement of symptoms of PPC will be compared using Cox proportional hazards regression with and without covariate adjustment (hazards ratio, 95% confidence intervals, *p* values). A Kaplan-Meier graphic representation of this analysis will be performed.

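### A PPC already present before allocation can be counted as a primary event, because the exclusion looks back only 24 h from screening while the outcome and the Cox clock run from surgery

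*Protocol article*

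**What the plan says.** Under Eligibility and exclusion criteria, the only bar to a prior PPC is "a PPC diagnosis anytime in the 24 h prior to eligibility screening". It is anchored on screening, reaches back 24 h and requires a diagnosis. The same list sets the outer limit for allocation by excluding "patients unable to be randomised by the research team within 48 h of surgery".

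Under Outcome measures, Primary outcome: "The primary outcome is the first occurrence of a PPC within the first 14 postoperative hospital days". Scoring is by calendar day: "A PPC will be diagnosed when four or more factors are present at any time from midnight to midnight on one postoperative day". For missed assessments, "retrospective collection of PPC data from the medical record will be permitted when a patient or assessor is unavailable for PPC assessment".

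Two statements date the event. The outcome section says "The day a PPC is first diagnosed is the day of onset for purposes of time-to-event analysis". Statistical methods says "the effect of time from the end of surgery/anaesthesia to commencement of symptoms of PPC will be compared using Cox proportional hazards regression". Neither refers to the time of randomisation. All outcomes are to be analysed by intention to treat, with no stated handling of a PPC whose onset precedes allocation.

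**The concern.** Three time references do not line up: the exclusion is tied to screening, allocation may come up to 48 h after surgery, and the outcome is counted from surgery. Where they leave a gap, a PPC that existed before the envelope was opened can be scored as a first occurrence. Treatment that had not yet been assigned cannot have prevented it. Counting such events adds a component to both arms that carries no information about the intervention, which moves the risk ratio towards 1 and lowers power in a trial planned at 80%.

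These participants also contribute little to the respiratory comparison, because "A confirmed PPC diagnosis ceases the respiratory treatment protocol". They do stay on the rehabilitation protocol of their allocated arm.

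**Working it through.** **The gap in time.** For a patient screened t hours after surgery, the look-back covers the period from t − 24 to t.

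- If t ≤ 24, the look-back reaches surgery, and any PPC diagnosed by then excludes the patient.
- If 24 < t ≤ 48, the first t − 24 hours after surgery lie outside it, at most 48 − 24 = 24 h. A PPC diagnosed in those hours does not exclude the patient unless it is diagnosed again inside the look-back.
- At any t, a PPC that is present but not yet diagnosed does not exclude the patient. Calendar-day scoring, or later scoring from the record, can then date it to the day of allocation or before.

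**The plan's own figure.** Inputs from Sample size: 20% control, 8% intervention, alpha 0.05, power 80%. Sidedness is not stated; I took two-sided. With the pooled normal approximation and mean rate 0.14:

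n = [1.96 × √(2 × 0.14 × 0.86) + 0.842 × √(0.20 × 0.80 + 0.08 × 0.92)]² / 0.12² = 130.1, rounded up to 131 per arm, or 262. This matches the protocol. Power at 131 per arm is 80.3%, with 131 × 0.20 ≈ 26 control and 131 × 0.08 ≈ 10 intervention events expected.

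**Dilution.** The document does not say how many PPCs predate allocation. Assume a share q of the 20% control PPCs does, equally in both arms, and that the planned 60% reduction applies to the rest:

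- control rate = 0.20
- intervention rate = 0.20q + 0.08(1 − q)

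**After the change.** If participants with an earlier PPC are excluded and events count only from randomisation, the control rate is 0.20(1 − q)/(1 − 0.20q) and the intervention rate is 0.4 times that. Power is again at 131 per arm.

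| q (assumed) | Early PPCs per arm (131 × 0.20q) | Rates as written | Ratio | Power as written | Rates after change | Power after change |
|---|---|---|---|---|---|---|
| 0 | 0 | 20% v 8.0% | 0.40 | 80.3% | 20% v 8.0% | 80.3% |
| 2% | 0.5 | 20% v 8.24% | 0.41 | 78.4% | 19.7% v 7.9% | 79.5% |
| 5% | 1.3 | 20% v 8.6% | 0.43 | 75.3% | 19.2% v 7.7% | 78.4% |
| 10% | 2.6 | 20% v 9.2% | 0.46 | 69.9% | 18.4% v 7.3% | 76.3% |

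At q = 5% the change recovers 78.4 − 75.3 = 3.1 points, and at q = 10% it recovers 76.3 − 69.9 = 6.4 points. It does not return to 80.3%, because excluding these patients also removes events.

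**The case against.** **The window is narrow, and that stands.** The Retrospective consent section describes randomisation as immediate on eligibility, and Randomisation and allocation has the envelope opened once a patient is deemed eligible. A PPC arising in a long interval between screening and randomisation is therefore not the planned course; 48 h is an outer limit from surgery. Surgery lists are screened daily, so many patients will have their whole postoperative period inside the look-back. A PPC that persists would often be diagnosed again within the 24 h and exclude the patient. In Table 3, low saturation and fever must be present on more than one consecutive postoperative day (with an automatic positive on saturation for some ventilated patients), and radiographs and sputum cultures are taken only when clinically indicated. Four criteria in the first hours will be uncommon. This limits the number of cases but does not close either route.

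**Same-day signs.** If some criteria were met before allocation and the fourth only afterwards, the threshold was reached after randomisation and the event is legitimate. Calendar-day scoring alone is not the fault.

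**Stronger readings that the documents do not support.** A reader might infer a bias in favour of one arm. Events before allocation are expected equally in both arms, so the expected effect is dilution. A reader might also infer a much larger loss by adding early PPCs in 5% of all participants on top of the planned rates. That gives 0.05 + 0.95 × 0.20 = 24.0% v 0.05 + 0.95 × 0.08 = 12.6%, ratio 0.53 and power 67%. It implies that 0.05/0.24 = 21% of control and 0.05/0.126 = 40% of intervention PPCs predate allocation, and nothing in the protocol suggests so many.

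**Late change.** Recruitment began in June 2015 and was expected to end in late 2018, and the article appeared in July 2018. Changing eligibility would affect only the last recruits. This is a fair reason to report the as-written count as well.

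**Conclusion.** The mismatch is in the text: as written, a PPC present before allocation can be counted as a primary event. The documents support can, not will, and give no count. The number is probably small. The consequence is conservative dilution: with 2% to 10% of control PPCs assumed early, the ratio moves from 0.40 to between 0.41 and 0.46, and power falls from 80% to between 78% and 70%. These figures rest on the assumed share, on equal occurrence in both arms, and on the planned 20% and 60% reduction holding for all other PPCs. The planned sample size reproduces and is not in question. I rate this a cheap improvement to the primary endpoint, not a flaw that threatens the validity of the comparison.

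**What to change.** 1. Define the primary outcome as the first PPC whose four-criterion threshold is first met after randomisation, up to postoperative day 14.
2. Start the time-to-event clock at randomisation, with one definition of onset. The day of first diagnosis and the start of symptoms are both named at present.
3. For remaining recruitment, extend the exclusion to any PPC diagnosed from the end of surgery to randomisation, checked in the medical record just before the envelope is opened.
4. For participants already randomised, specify before unblinding, identically in both arms, an analysis that leaves out those whose recorded PPC onset precedes allocation. Report the as-written count alongside.

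The cost is one criterion, one sentence of the outcome definition, one of the analysis text, and a short record check. Since onset is recorded by day, a PPC on the day of allocation also needs the clock time at which the threshold was met. A few patients become ineligible and the event rate falls slightly, so part of the gain is lost: if 5% are early, power is about 78%, not 80%.

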### Randomisation and allocation

An administrative assistant independent of the trial will prepare 288 consecutively numbered (1 to 288) opaque envelopes each containing an allocation card wrapped in extra paper or aluminium foil [14]. Allocation sequence is determined by a computer-generated (http://www.randomizer.org/) blocked random number table (6 blocks of 48) with large blocks to minimise guessing of allocation sequence. The randomisation table will be sealed in an opaque envelope, locked within the primary centres’ research institute, and made unavailable to trial personnel until trial completion. The number of consecutively numbered envelopes provided to each site will be dependent on funding agreements (i.e. funded to recruit one block of 48 participants, or, on a per patient recruit basis till the end of the trial).

Once a patient has been deemed eligible, the treating ward physiotherapist receives the group allocation by first writing patient details on the next consecutively numbered sealed opaque envelope and then opening it. If numerous new patients are eligible on the same day at a site, envelopes will be allocated in alphabetical order of surname. If an envelope is not available at the time of randomisation, a coin can be tossed by the treating physiotherapist and the result written on a card and countersigned by an independent observer. This card will be placed within the envelope that should have been allocated for that patient. If an envelope is erroneously opened out of sequence, the reason for doing so will be documented on it and the patient will be treated as per allocation card. Any aberrations to sequential allocation will be recorded. Envelopes will be kept securely by the ward physiotherapist or site investigator until hospital discharge and then integrated with the consent form and filed securely by the site investigator. Potential selection bias will be studied by extracting basic demographic data and planned surgical procedure from the medical records of all included and excluded patients.

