### Blinding

The recruiting and treating physiotherapists will be solely aware of group allocation. Assessments of primary and secondary outcomes and data collection will be performed by independent masked assessors not involved in the participant’s care. Assessors will require access to the medical record. To ensure masking to group allocation, documentation of physiotherapy assessments and interventions will be written to a standardised format (Additional file 5) with treatment recorded ‘Treatment provided as per ICEAGE protocol’. Documentation detailing physiotherapy treatment will be recorded separately and stored securely by the treating physiotherapist until the 14th postoperative day, the day of discharge, or until a defined endpoint is met, whichever occurs first, at which point the physiotherapy treatment documentation will be integrated into the medical record.

All doctors, surgeons, nurses, discharge coordinators, data analysts, and statisticians will be blinded to group allocation. If a participant inadvertently informs an assessor of their specific physiotherapy treatment, this will be reported, and a new assessor will be found for ongoing assessments.

It is anticipated that participants will be blinded to group allocations as both arms receive physiotherapy. A convenience sample of 30 consecutive participants will be asked which group they believed they had been allocated at the 90-day follow-up interview.

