The principal site investigator will approach the patient from the fourth postoperative day and describe the trial, including the potential risks and benefits, and involvement required from the patient. Written information will be provided, and the patient will be invited to participate in the trial. Any person not consenting following randomisation is withdrawn from the trial. If the patient consents to continue in the trial, they will sign a consent form as required by local ethics committees and in accordance with the Declaration of Helsinki. If the patient remains in a state where informed consent is unable to be provided, (i.e. unconscious, delirious, nauseated, pain, repeat surgery) the next of kin will be contacted for consent. If the patient or next of kin declines to participate, the patient will take no further part in the trial and all data will be withdrawn. Physiotherapy will then be provided to them at the discretion of the ward physiotherapist.

Trial participants will have the autonomy to decline any therapy session as per standard care provision and medico-legal requirements regardless of recruitment into the trial. Reasons for non-participation in therapy sessions will be documented.

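### The site investigator, whom the protocol calls blinded, may hold the opened allocation envelope during the hospital stay while also raising tests for a possible PPC and perhaps seeking consent

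*Protocol article*

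**What the plan says.** The section on randomisation and allocation states that "the treating ward physiotherapist receives the group allocation by first writing patient details on the next consecutively numbered sealed opaque envelope and then opening it". The opened envelope therefore identifies the patient and contains the allocation card. The section continues: "Envelopes will be kept securely by the ward physiotherapist or site investigator until hospital discharge and then integrated with the consent form". After that, envelope and consent form are "filed securely by the site investigator". Resealing and a separate custodian are not mentioned.

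The Blinding section restricts knowledge of the arm: "The recruiting and treating physiotherapists will be solely aware of group allocation". It has the treating physiotherapist store the detailed treatment records apart from the medical record until day 14, discharge or a defined endpoint, whichever comes first.

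The section on the primary outcome requires four of eight criteria for a PPC. When three are present, "the blinded site investigator or ward physiotherapist will discuss the option of further diagnostic testing to confirm PPC" with the treating physician.

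The section on retrospective consent says that "The principal site investigator will approach the patient from the fourth postoperative day and describe the trial". This follows randomisation and several days of allocated treatment. If the patient or next of kin declines, "the patient will take no further part in the trial and all data will be withdrawn".

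**The concern.** One role is called blinded in one section and is allowed in another to hold an opened card that names the arm. The role matters because it acts at a point that can affect the primary outcome. A patient with three criteria is one short of a PPC. Chest radiographs, white cell counts and sputum cultures are not scheduled by the trial, so a suggestion to test can decide whether a fourth criterion is ever found. If the person who makes it can know the arm, prompting may differ between arms.

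The second point is consent. It is sought after allocation, and a refusal deletes the patient's data. If the person presenting the trial can know the arm, the way it is presented, and so the refusals, could depend on arm. An intention-to-treat analysis cannot recover patients whose data have been withdrawn.

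**Working it through.** The article gives no figure on this point, so the check sets its statements side by side.

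1. **Is the arm readable from the envelope?** Yes. Patient details are written on the outside and the envelope is then opened. Nothing in the text closes it again.

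2. **Who may hold it during the stay?** The ward physiotherapist or the site investigator. The second is permitted, not required.

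3. **Who has it after discharge?** The site investigator files it, and no other role is named. By then in-hospital PPC assessment is over and consent has usually been sought. The period that matters is therefore the hospital stay, where custody by the site investigator is optional.

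4. **Is the site investigator allowed to know the arm?** Two readings are possible.
   - The site investigator is not a recruiting or treating physiotherapist. The Blinding section then excludes that role from knowing the arm, and the custody rule conflicts with it.
   - The site investigator counts as a recruiting physiotherapist. The role may then know the arm, and the word blinded in the primary-outcome section is wrong.

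   On either reading one statement has to change.

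5. **Does the role affect the primary outcome?** Indirectly. At three of eight criteria it may raise further testing with the treating physician. It does not score the criteria or confirm the PPC.

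6. **Who else may raise testing?** The same sentence names the ward physiotherapist. If the adjective blinded covers both roles, this must be someone who is not treating that patient. If it covers only the site investigator, the person who opened the envelope may prompt the test with certain knowledge of the arm. The text does not settle this.

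7. **Does the role seek consent?** The consent section names the principal site investigator, and the other two sections name the site investigator. The article neither equates nor separates them, so the consent part of the point is conditional on their being the same person.

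**The case against.** The strongest reply is that this is one loose phrase. Custody by the site investigator during the stay is an alternative, the envelope is to be kept securely, and nothing says that the holder reads the card. All of that stands. It means the procedure permits access and does not show that access occurs. Resealing could also be described in a fuller protocol that is not shown. The conflict between the sections is nevertheless in the article itself.

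A reader might infer that assessor blinding fails. The documents do not support this. Daily PPC assessment is given to blinded assessors, a blinded senior physiotherapist confirms any suspected PPC, and the Blinding section places outcome assessment with masked staff who have no part in the patient's treatment. No route from envelope to assessor is shown. The testing route is also damped, because the site investigator only raises an option and the physicians who order tests are masked.

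A reader might also infer that filing the envelope at discharge endangers the 90-day interviews. That does not follow. Nothing says that interviewers see the filed consent form. The Blinding section in any case releases the treatment records into the medical record by discharge at the latest, so later filing of the envelope would not close that route.

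Finally, it can be said that site investigators recruit, since "Local investigators will screen daily surgery lists and recruit eligible patients from the ICU and wards at participating hospitals", and so may know the arm. That reading removes the conflict with the Blinding section but leaves the word blinded in the primary-outcome section unsupported.

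**Conclusion.** The point holds in a narrow form. As written, the custody rule permits a role described as blinded to hold a readable, patient-identified allocation card during the period in which that role may prompt testing. This contradicts the primary-outcome section and, unless site investigators count as recruiting physiotherapists, the Blinding section as well. The consent part holds only if the principal site investigator is the same person.

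The possible consequences are arm-related prompting of tests and arm-related exclusion after randomisation. Their size cannot be derived from the article. It does not say how many envelopes site investigators hold, how many patients reach three criteria, or how many decline consent. The stronger statement, that allocation necessarily reaches the site investigator while PPCs are being assessed, is not supported, because custody before discharge is optional. Correction is still worthwhile: the remedy is nearly free, and recruitment was continuing when the article was published.

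**What to change.** In the allocation procedure, delete the site investigator as an alternative holder of the envelope. The treating physiotherapist reseals the card, keeps it with the separately stored treatment records, and passes it on for filing only after that patient's 14-day PPC assessment and consent are both complete. State this release point explicitly: the treatment records may be released earlier, when a defined endpoint is met, and the card should not go with them.

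In the primary-outcome section, require that the prompt for further testing comes from a blinded person who has not handled the envelope. This can be the blinded site investigator or a ward physiotherapist who is not treating that patient. In the consent section, apply the same condition to whoever seeks consent.

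The cost is a short edit in three sections, secure storage with the treating physiotherapist, and a narrower choice of who may raise testing. The treating ward physiotherapist could no longer do so for their own patient within the trial's prompt. No extra staff are needed. The change closes the envelope route only and does not alter when treatment records enter the medical record.
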